### Participant timeline {13}

Figure 4 shows the participant timeline.

**Fig. 4 Fig4:**
[figure not shown]
Time schedule of enrollment, interventions, and assessments

### Sample size {14}

Sample size estimates were based on our team’s preliminary data for CBT-I intervention for adolescents [14, 15], Internet-delivered CBT-I for adults [23, 25], our WebMAP trials [16, 17], and other trials of CBT-Pain in youth with headache or migraine [8, 37, 38]. Based on these preliminary data, power analyses indicated that 77 subjects per group would provide 80% power to detect a moderate effect size (Cohen’s *d* = 0.45) on the primary sleep outcome of insomnia symptoms (ISI [27]) and the primary headache outcome of headache-related disability (CALI-9 [31]). Attrition in our prior web-based trials has been less than 10% [16, 17]. With attrition conservatively estimated at 15%, we expect to enroll 180 subjects to achieve a final sample size of 154 subjects.

### Recruitment {15}

Patients will be recruited from the Seattle Children’s Hospital Neurology Clinic, which carries out over 700 outpatient visits for headaches annually. We estimated an approximate rate of youth with co-morbid migraine and insomnia using data from the 240 participants with migraine recruited into a prior study in this clinic; 71% met the criteria consistent with a positive screen for insomnia [3]. Thus, we conservatively expect 40–50% of referrals to be eligible based on the inclusion and exclusion criteria. In our prior web-based trials, participation rates have been over 50% [16, 17]. Therefore, we anticipate needing to screen 360 patients to recruit 180 patients.

### Assignment of interventions: allocation

#### Sequence generation {16a}

Participants will be randomly allocated to the two study arms in a 1:1 ratio. To further balance the arms, randomization will be blocked with block sizes varying from 4 to 10. An independent data manager not involved in other study procedures will generate the allocation sequence using computer-generated random numbers.

#### Concealment mechanism {16b}

The allocation sequence will be implemented using the REDCap randomization framework [39], which ensures that the allocation sequence remains concealed until interventions are assigned.

#### Implementation {16c}

After completing informed consent, assent, and the pre-treatment assessment, the study staff will use the REDCap randomization framework to allocate the participant to one of the study arms. Different study staff will generate the allocation sequence, conduct participant enrollment, and assign participants to interventions.

### Assignment of interventions: blinding

#### Who will be blinded {17a}

Only the study staff who assigns participants to interventions will be unblinded to the treatment assignment. All other study staff will be blinded to the treatment assignment, including outcome assessors, data analysts, and investigators. This will be achieved by restricting access to participants’ treatment assignments in our tracking database so that it is only viewable by the study staff whose role is to assign participants to interventions. Trial participants and care providers will not be told which intervention arm was assigned to individual patients, so they will also be blinded to treatment assignment.

#### Procedure for unblinding if needed {17b***}***

Unblinding is permissible in the unlikely event that an adverse event occurs. In that case, the study coordinator who assigns participants to interventions would inform the study investigators of the participant’s intervention assignment.

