#### Criteria for discontinuing or modifying allocated interventions {11b}

Participants can discontinue the trial procedures and request to be removed from the trial at any time. Study investigators can discontinue a patient’s participation in the study if they do not complete the pre-randomization/baseline assessment, or upon new presentation of exclusion criteria (e.g., inpatient hospitalization, diagnosis of a new serious medical condition). Data that have been collected prior to discontinuation will be included in analyses. This is a low-risk behavioral trial, and adverse events are expected to be minor; therefore, there are no planned criteria for premature study termination or for modifying allocated interventions.

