### Outcomes {12}

The primary outcome following treatment phase 1 is change in self-reported insomnia symptoms (Insomnia Severity Index (ISI) [27]) from pre-randomization/baseline to immediately after treatment phase 1, immediately after treatment phase 2, and 6-month follow-up. The ISI has shown strong validity and reliability estimates, including sensitivity to change in response to insomnia treatment for teens with physical and mental health comorbidities [14, 15]. Secondary outcome measures of sleep include self-reported sleep quality (Adolescent Sleep-Wake Scale-Short Form (ASWS-SF)) [28] and sleep patterns (sleep duration, sleep efficiency, and wake after sleep onset) assessed using 14 days of daily sleep diary and actigraphic monitoring (Actiwatch Spectrum Plus, Phillips Respironics, Bend, OR) [29, 30].

The primary outcome following treatment phase 2 is change in activity limitations due to headache (Child Activity Limitations Interview-9 (CALI-9)) [31] from baseline to phase 1 post-treatment, phase 2 post-treatment, and 6-month follow-up. The CALI-9 measures difficulty in performing usual daily physical, social, and recreational activities (e.g., going to school, participating in activities at home) due to headache and has demonstrated sensitivity to change in response to CBT-pain treatment. Adolescents will complete a 14-day electronic diary which includes (1) the CALI-9 diary version [32], (2) the presence of headache (yes/no) to compute headache frequency [33] (secondary outcome), and (3) headache pain intensity (11-point Numerical Rating Scale (NRS)) [34] (secondary outcome). Additional secondary outcomes include self-reported emotional functioning (PROMIS Pediatric Anxiety and Depression short form scales v.2.0) [32] and health-related quality of life (youth self-report Pediatric Quality of Life Inventory 4.0) [35].

Adolescents and parents will complete a Treatment Experience Survey adapted for this study [36] concerning whether they experienced negative effects of study participation (e.g., worrying about sleep or pain, overwhelmed with treatment assignments, tension at home) and rate the level of discomfort experienced (0 = did not affect me/my teen at all, 3 = affected me/my teen very negatively). The number, type, and severity of negative experiences will be summarized. Participants will also report adverse events via free text response at each assessment time point.

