#### Composition of the data monitoring committee, its role, and reporting structure {21a}

In agreement with the Seattle Children’s Research Institute IRB and the NIH/NICHD, a DSMB has not been appointed for this study. This study is not considered a NIH-defined phase III clinical trial. Furthermore, the assessments and behavioral interventions have been used previously by the study investigators in our prior research and clinical work. The risks of the interventions are known, and they are minimal. Moreover, participation in this study is adjunctive to routine treatment through the Seattle Children’s Hospital Neurology Clinic, and thus, participants will be monitored by their treating physicians. Treatment in the neurology clinic will not be altered by study participation. A neurologist knowledgeable in the field of pediatric headache and insomnia and a biostatistician knowledgeable in pediatric clinical trials will be assigned as data and safety officers for this study. In the case of suspected adverse events, they will be contacted to assess whether the suspected adverse event is related to treatment and will recommend the next steps for safety measures when indicated.

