#### Adverse event reporting and harms {22}

The study staff will have frequent interactions with participants (1–2 times per week) during the intervention period to monitor program completion and to evaluate any unwanted treatment reactions or adverse events. In addition, at each of the post-treatment assessment time points, participants will complete the Treatment Experiences Survey which is a self-report scale that assesses unwanted changes in sleep, pain, and stress as a result of study participation. Responses that indicate a potential adverse event or unanticipated event that may be related to the study protocol will be escalated to the PI within 48 h of identification and will be reviewed with the study’s data and safety officers. Adverse events that are determined to be a result of study participation will be reported to the IRB and the funding agency (NIH/NICHD). In the event that a participant withdraws from the study or is discontinued due to a serious adverse event, the participant will receive follow-up monitoring by the study staff until the problem has been resolved or stabilized or is determined to be unrelated to the study. All adverse events, serious and non-serious, will also be reported annually to the IRB during the yearly renewal process.

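### The unblinding rule lets any adverse event, however minor, release a participant's arm to investigators who are meant to be blinded

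*Protocol article*

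**What the plan says.** Section {17a} of the Protocol article leaves only the assigning staff unblinded: "All other study staff will be blinded to the treatment assignment, including outcome assessors, data analysts, and investigators".

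Section {17b} gives the exception: "Unblinding is permissible in the unlikely event that an adverse event occurs". The recipients are stated too: "the study coordinator who assigns participants to interventions would inform the study investigators of the participant’s intervention assignment". The exception carries no qualifier for seriousness, severity, relatedness or need to know.

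On collecting events, section {12} states: "Participants will also report adverse events via free text response at each assessment time point". Section {22} adds staff contact once or twice a week during the intervention period, partly to look for unwanted reactions and adverse events, and a survey of negative effects at each post-treatment assessment. It also provides for annual reporting of adverse events to the IRB, covering serious and non-serious events alike.

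On handling events, section {22} says that responses pointing to a possible study-related event "will be escalated to the PI within 48 h of identification and will be reviewed with the study’s data and safety officers". Section {21a} gives the causality question to those officers: "they will be contacted to assess whether the suspected adverse event is related to treatment".

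**The concern.** An unblinding rule should open the code when someone must know the arm to deal with what has happened. Here the condition is only that an adverse event has occurred. A non-serious event whose management does not depend on the assigned program meets it just as a serious one does.

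The recipients matter as well. The study investigators, named as a group, include the principal investigator, who receives escalated events and takes them to the data and safety officers. Events judged to result from participation then go to the IRB and the funder. Whether an event was caused by the program is a judgement that knowledge of the arm can sway. If the principal investigator already knows the arm, that knowledge can enter the discussion before the officers decide. Section {6b} names masking of allocation as one purpose of the education control, so a loose exception also weakens a stated reason for that comparator.

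**Working it through.** No figure in the plan bears on this point, so there is none to reproduce. The check is a reading of the sections against each other.

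1. **Is the trigger narrowed anywhere?** Sections {11b}, {12}, {17a}, {17b}, {21a}, {22} and {30} were compared. None limits unblinding to serious, related or arm-dependent events.

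2. **Do non-serious events count as adverse events?** Yes. Section {22} uses the term for both kinds. Section {11b} says "This is a low-risk behavioral trial, and adverse events are expected to be minor", and section {30} repeats the expectation. These describe how severe events would be, not how often they would occur.

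3. **How many occasions are there to detect an event after randomization?**
   - Assessments: four, less baseline, which precedes randomization (section {16c}): 4 − 1 = 3.
   - Contacts: each phase delivers six cores at one per week, so 6 weeks. At 1 to 2 contacts per week this is 6 × 1 = 6 to 6 × 2 = 12 per phase. Assuming that the intervention period covers both phases, the total is 2 × 6 = 12 to 2 × 12 = 24.
   - Total: 3 + 12 = 15 to 3 + 24 = 27 occasions per participant.

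   These are opportunities for an event to surface, not a count of events or unblindings. They show that a trigger worded for a rare exception sits beside an active search for events.

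4. **Who learns the arm, and what do they do?** The investigators learn it. Under section {22} the principal investigator receives escalated events within 48 hours and reviews them with the officers. Under section {21a} the officers assess relatedness. No order is fixed between disclosure and that assessment, so disclosure may come first.

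5. **Can the arm reach the primary results by this route?** Hardly.
   - The ISI and CALI-9 are adolescent self-reports (Table 1), completed online in private (section {18a}).
   - Outcome assessors and data analysts are not recipients under section {17b}.
   - Section {20c} analyses everyone randomized.
   - Section {11b} says "Study investigators can discontinue a patient’s participation in the study", but on two grounds only. An incomplete baseline arises before there is an arm to know. The other, newly presenting exclusion criteria, is illustrated by hospitalization and new serious illness.
   - Section {18b} still invites those who do not complete the intervention to follow-up.

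6. **Can the number affected be computed?** No. It would be 180 multiplied by the proportion with an adverse event, and that proportion is not given.

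**The case against.** The strongest reply is that section {17b} only permits unblinding, under a heading that says it is for use if needed. A blinding rule followed by an exception is normal structure and no contradiction, and need-to-know criteria and a log are details that an article may leave to the full protocol. Much of this stands: unblinding is not automatic, and the absence of a log from the article is no fault. But the article does not leave the trigger and the recipients to another document. It states both, and states them too broadly.

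Several stronger readings are tempting and are not supported:

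- *That minor events are expected and will routinely break the blind.* The plan predicts that events will be minor if they occur, and section {17b} calls them unlikely. The negative-effects survey in section {12} is summarized separately from free-text adverse events, so an ordinary complaint of stress is not thereby an adverse event.
- *That the treatment comparison or discontinuations will be biased.* The safeguards in step 5 leave little room for that.
- *That the exposure is known to be unequal between arms.* Only the CBT-I program includes sleep restriction, but no difference in complaints is documented. A complaint specific to that component could in any case hint at the arm whatever section {17b} says.
- *That a definite number of participants would be unblinded.* Any count rests on an assumed event rate and would measure permission, not practice.

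**Conclusion.** The point holds as a rule stated too broadly. Any adverse event is enough to allow disclosure of the arm to investigators whom the plan otherwise blinds, and nothing in the article ties disclosure to need. The avoidable exposure lies in the principal investigator's handling of escalated events, the review preceding the relatedness judgement, and the accuracy of the blinding claim. Bias in the two primary outcomes from this source is likely to be small. The size cannot be stated as a number.

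The conclusion rests on reading adverse event in section {17b} as section {22} uses it, serious and non-serious alike, and on no narrower rule being stated in the article. The article does not say whether the data and safety officers are themselves blinded, so it does not establish that relatedness is currently judged without knowledge of the arm. The change is worth making because it is cheap, not because the main results depend on it.

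**What to change.** Reword section {17b} on four points:

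- **Trigger.** Allow unblinding of an individual only when the arm must be known to manage the event, for example a serious adverse event or a determination by the existing data and safety officers that the arm is needed.
- **Order.** Where feasible, have relatedness recorded before the arm is disclosed.
- **Recipients.** Limit disclosure to those who need the arm for that event. Other investigators, outcome assessors and analysts stay blinded.
- **Record.** Log each unblinding with date, reason and recipient, and report the counts by arm.

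A sentence in section {17a} pointing to this exception would join the two sections. The cost is protocol wording, a short log and one extra step before an investigator learns the arm. The officers are already provided for in section {21a}. Interventions, outcomes, sample size and analyses are unchanged.

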### Data collection and management

#### Plans for assessment and collection of outcomes {18a}

The primary source of data will come from questionnaires and daily diaries which will be completed online using REDCap. Adolescents and parents will complete online assessments privately and independently. Adolescents will also be sent an actiwatch via postal mail to their homes, which they will wear for 14 days and then return to the study staff via postal mail. The study staff will use an electronic database management system to track the administration of assessments. The database will be password protected and stored on a secure server that is only accessible to the study staff. Monthly audits of the database will be conducted to monitor adherence to the study protocol. See Table 1 for the description of the study instruments.

**Table 1 Tab1:** Primary and secondary outcome measures

	Measure description	Respondent
**Primary outcomes**		
Insomnia symptoms	The 7-item Insomnia Severity Index measures the severity and impact of insomnia symptoms. Items are rated on a 5-point Likert scale (0–4) and summed to create a total score. Total scores above 8 indicate clinically significant insomnia symptoms in adolescents and adults.	Adolescent
Headache disability	The CALI-9 is a validated self-report measure of daily pain-related disability in children and adolescents completed daily for 14 days. The 9-item measure assesses the difficulty in performing usual daily physical, social, and recreational activities due to headache. Total scores range from 0 to 100, with higher scores indicating greater headache-related disability. Average scores over each 14-day measurement period will be computed.	Adolescent
**Secondary outcomes**		
Sleep quality	The Adolescent Sleep Wake Scale-Short Form is a 10-item measure of sleep quality. The total score reflects the overall perception of sleep quality.	Adolescent
Sleep patterns	Minutes of estimated sleep, wake time after sleep onset, and sleep efficiency are calculated from actigraphic monitoring over 14 days with the Actiwatch Spectrum Plus.	Adolescent
Headache frequency	The number of headache days reported each day for 14 days.	Adolescent
Headache pain intensity	11-point numerical rating scale with anchors of 0 = no pain and 10 = worst pain possible. Reported daily for 14 days.	
Anxiety symptoms	The Generalized Anxiety Disorder-7 is a 7-item measure of anxiety symptoms. The total score indicates anxiety severity over the last 2 weeks.	Adolescent
Depressive symptoms	The Patient Health Questionnaire-9 is a 9-item measure of depressive symptoms. The total score indicates the severity of depressive symptoms over the last 2 weeks.	Adolescent
Health-related quality of life	The Pediatric Quality of Life Inventory 4.0 is a measure of health-related quality of life. The total score indicates perceived physical and mental health.	Adolescent

#### Plans to promote participant retention and complete follow-up {18b}

Participants will receive detailed information about the study protocol during recruitment and enrollment and will receive emails, text messages, and telephone reminders from the study staff to complete follow-up assessments. Participants will also be provided with an e-commerce gift card after completing each assessment. Questionnaire measures and daily diaries are completed online so that participants can complete these at a time and place that is convenient for them. All survey responses are saved so that participants do not have to complete questionnaire measures in a single sitting. All participants will be invited to complete follow-up assessments, including those who do not complete the intervention.

#### Data management {9}

##### Questionnaire measures and daily diaries

Questionnaire measures and daily diaries will be collected online via REDCap, which automatically alerts the participant and study staff to missed or implausible responses. To ensure complete data, the study staff will follow up with participants when missing data are identified. Scoring errors will be minimized by the use of syntax to autoscore the questionnaire responses and conduct range checks for data values. The output will be downloaded and stored on our secure server that is only accessible to the study staff.

##### Actigraphy monitoring

Adolescents will complete 14 days of actigraphy monitoring to assess sleep patterns using the Actiwatch Spectrum Plus (Philips Respironics, Bend, OR, USA), a watch-like device worn on the non-dominant wrist that records sleep-wake patterns based on movement detected by an omnidirectional sensor. Participants will also (a) push an event marker on the Actiwatch at bedtime and when they wake in the morning and (b) complete a corresponding daily electronic sleep diary each morning to report on the prior night’s sleep pattern (bedtime, wake time, number and duration of night wakings). To ensure data quality, a standardized actigraphy scoring protocol will be followed. Data will be scored in 1-min epochs using the Philips Actiware version 6.2.0 software (Philips Respironics, Bend, OR, USA). To minimize scoring errors and ensure the validity of actigraphy data, event markers and sleep diary data will be used to assist with scoring decisions.

Three actigraphy variables will be calculated for analyses: (1) total sleep time—the total amount of time scored as sleep in minutes from sleep onset to sleep offset, with sleep onset defined as the first 10-min segment with no more than one epoch of any recorded activity and sleep offset defined as the last 10-min segment with no more than one epoch of any recorded activity; (2) wake minutes after sleep onset—the number of minutes scored as wake after nighttime sleep onset; and (3) sleep efficiency—the ratio of total sleep time and total time spent in bed at night as a percentage, with values closer to 100 indicating more efficient sleep [30].

#### Confidentiality {27}

Contact information for potential participants will be sent by referring providers to the study staff via a secure internal message in the Seattle Children’s Hospital electronic health record. Identifying information and research data will be stored separately on encrypted, secure, password-protected databases on Health Insurance Portability and Accountability Act (HIPPA)-compliant servers at Seattle Children’s Research Institute. Research data will be coded with a unique identifier, and no personal identifiers will be present among research data. The code that links identifying information to study identifiers will be accessible only to the study staff. All research data will be deidentified at the earliest possible opportunity to promote data sharing.

